### 2.2. Trial Design

This will be a safety study of FMT for the prevention of NEC, in the form of a prospective, open-label study with continuous recruitment of up to 40 patients in total (20 in the study group, 20 in the control group). Included patients must meet the exact inclusion criteria described below and must not meet any exclusion criteria. The study group will include 10 premature infants born between 28 0/7 and 36 6/7 weeks of gestation, followed by another 10 premature infants born between 24 0/7 and 27 6/7 weeks of gestation, and 20 premature infants in the control group. After completion of this stage (inclusion and treatment of 20 patients + 20 in the control group), the safety of the therapy will be assessed with a description and presentation of all adverse events, their classification and relationship to the intervention.

The safety of the therapy will be assessed by comparison with a control group, i.e., 20 patients who will meet the same inclusion criteria and will not meet any of the exclusion criteria, subject to the same hospital observation but without undergoing any medical/therapeutic intervention other than the collection of biological material (including stool, blood and urine samples for exploratory testing of the gut microbiota).

Recruitment will occur continuously between January 2026 and January 2027. The study is registered at ClinicalTrials.gov (NCT06333405).

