### 4.3. Monitoring the Transplant Recipients After the Procedure

Based on experience with FMT, the highest risk of developing sepsis, a rare but dangerous complication, occurs within the first six hours after the preparation is administered. Therefore, after the procedure, the patient will be continuously monitored.

The following will be assessed for the next 72 h after FMT administration:The number of episodes of oral feeding intolerance, diarrhea and the presence of blood, mucus or pus in the stool.The appearance of symptoms of infection or significant changes in vital signs (ECG, heart function and saturation—continuous measurement; blood pressure—4 times a day; temperature).The number of cases of NEC developed.Observation of other symptoms, such as convulsions, inconsolable crying and anxiety.The number of positive blood cultures and the percentage of antibiotic therapy use.Number of serious adverse events (SAEs), e.g., death, serious threat to health and/or life, and/or deterioration of health.

Blood inflammation parameters (leukocyte count, CRP and procalcitonin) will be collected before administration of the preparation (FMT1) and no later than 6–12 h after administration of FMT2, then every 12–24 h up to 72 h after FMT, depending on the patient’s condition.

A blood culture will be taken in the event of a significant increase in inflammatory parameters.

If any of the above-described criteria for temporary postponement of microbiota administration occur between FMT1 and FMT2 but resolve within 6 h (reassessment of the child’s condition after a minimum of 6 h) and do not recur within the next 6 h, the second dose of microbiota (FMT2) may be administered.

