### 4.4. Procedures for the Patients in the Control Group

Check whether the patient meets the inclusion criteria for the experiment.Check whether the patient meets the exclusion criteria.Discuss the purpose and procedures of the experiment with the patient’s parents/guardians and obtain their informed consent for the child’s participation in the experiment. This includes consent for the processing of personal data and the use of biological material samples for scientific purposes, as well as consent for participation in surveys and follow-up on the effectiveness of therapy.Collect blood parameters indicating inflammation (leukocytosis, CRP, procalcitonin) at the “0” point (“BEFORE intervention”), between signing the consent form and the fifth day of the child’s life.Ensure that biological material samples (feces, urine and blood samples) are collected before (point “0”) FMT, as described in the section below, or collect samples before the sixth day of the child’s life.For the control group, the matching time point for administering gut microbiota doses and counting “post” days is assumed to be the sixth day of the child’s life.From day 6 (the matching time point), any adverse events or deviations from the norm will be recorded, such as deterioration in general condition, appearance of symptoms of infection or increase in inflammation indicators.Blood inflammation parameters (leukocytosis, C-reactive protein (CRP), procalcitonin) will be collected during the “post-matching time point” period at least once within 72 h of day 6, or more frequently if the patient’s clinical condition requires it, as assessed by the attending physician.

The following will also be recorded in both study groups:-The number of days spent in hospital;-Percentage increase in body weight (birth weight vs. weight at discharge);-The number of days of antibiotic therapy received during hospitalization (monitoring until discharge from the hospital conducting the experiment).

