## 5. Expected Results

### 5.1. Primary Outcome

The primary outcome is safety, assessed through adverse event reporting and comparison with the control group.

Examination of the safety profile includes analysis of all adverse events, including any deviations from the norm: deterioration in general condition, appearance of symptoms of infection, and increase in inflammation indicators.

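### Inflammation panels and the 72 h checklist are scheduled unequally between arms, yet a marker rise counts as a primary adverse event, so the comparison may be biased against FMT

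*Protocol article*

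**What the plan says.** **FMT arm (section 4.3).** After a baseline panel, inflammation markers are taken "no later than 6–12 h after administration of FMT2, then every 12–24 h up to 72 h after FMT", with the frequency made dependent on the infant's condition. A significant rise leads to a blood culture. A list of feeding, stool, vital-sign, infection, NEC, neurological, culture, antibiotic and SAE items is introduced by "The following will be assessed for the next 72 h after FMT administration".

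**Control arm (section 4.4).** After a baseline panel, markers are taken "at least once within 72 h of day 6, or more frequently if the patient’s clinical condition requires it, as assessed by the attending physician". Clinical capture is general: "From day 6 (the matching time point), any adverse events or deviations from the norm will be recorded". There is no itemised 72 h list and no stated culture trigger.

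**Endpoint and analysis.** Section 5.1 defines the safety analysis as covering all adverse events, "including any deviations from the norm: deterioration in general condition, appearance of symptoms of infection, and increase in inflammation indicators". Section 2.3.3 compares the proportion with at least one AE or SAE by Fisher's exact test. It does the same for specific AEs, and gives relative risks with 95% intervals.

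**What is claimed about observation.** Section 2.2 describes controls as "subject to the same hospital observation but without undergoing any medical/therapeutic intervention" beyond sample collection. The limitations in section 5.4 speak of parallel observation in both groups. They acknowledge detection bias only as a consequence of open-label assessment, and name CRP and blood cultures among the objective measures that mitigate it.

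**The concern.** An endpoint of the form 'ever flagged' rises with the number of times one looks. If one arm has a repeat panel schedule by default and the other needs a single panel, the first arm will tend to accumulate more marker-rise events even when the treatment does nothing. The FMT-only culture trigger and the FMT-only checklist act in the same direction.

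The hypothesis in section 2.1 is that the event profile is comparable to standard care, and section 2.3.1 says the event rates are meant to inform a later randomised trial. Unequal ascertainment harms both aims. A harmless product could appear to carry a safety signal, or a real signal could be explained away as a testing artefact. The limitations section does not cover this, because CRP panels and the cultures they trigger are themselves scheduled unequally.

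**Working it through.** The plan gives no power or sample-size figure (section 2.3.1), so there is none to reproduce.

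**Inputs from the protocol article.** First FMT panel at t0 = 6 to 12 h after FMT2; repeat interval d = 12 to 24 h; end at 72 h (4.3). Control minimum of one panel (4.4). 20 infants per arm (2.2). Fisher's exact test, two-sided 0.05 (2.3.3).

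**Assumptions, not in the documents.** The chance p that one panel shows a rise unrelated to treatment; the within-infant correlation ρ; the background chance B of any other AE, equal in both arms.

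**Step 1: number of scheduled panels,** k = 1 + floor((72 − t0)/d).
- t0 = 6, d = 12: 1 + floor(5.5) = 6. t0 = 12, d = 12: 1 + 5 = 6.
- t0 = 6, d = 24: 1 + floor(2.75) = 3. t0 = 12, d = 24: 1 + floor(2.5) = 3.

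If the 72 h run from FMT1, the window ends 66 h after FMT2. The range is still 3 to 6, with 5 for a 12 h start and 12 h interval. The scheduled contrast is 3–6 versus 1.

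**Step 2: marker-rise event alone, no FMT effect, independent panels.** Share flagged = 1 − (1 − p)^k. The last column is the chance that Fisher's test shows significant harm, by full enumeration of both binomials.

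| p | FMT, k = 3 to 6 | Control, k = 1 | RR | False harm |
|---|---|---|---|---|
| 5% | 14.3% to 26.5% | 5% | 2.9 to 5.3 | 6% to 34% |
| 10% | 27.1% to 46.9% | 10% | 2.7 to 4.7 | 18% to 67% |
| 20% | 48.8% to 73.8% | 20% | 2.4 to 3.7 | 38% to 90% |

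At p = 10% this is 5.4 to 9.4 infants of 20 against 2.0. With one panel in each arm the RR is 1.0 and the chance of false harm is 0.6%.

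**Step 3: allow correlation within an infant.** Beta-binomial with a = p(1/ρ − 1), b = (1 − p)(1/ρ − 1). The chance of no flag in k panels is the product of (b + j)/(a + b + j) for j = 0 to k − 1. At p = 10%:
- ρ = 0.3: 20.8% (k = 3) to 29.4% (k = 6), RR 2.1 to 2.9, false harm 8% to 23%.
- ρ = 0.6: 15.8% to 19.4%, RR 1.6 to 1.9, false harm 3% to 6.5%.

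**Step 4: proportion with any AE.** Share = 1 − (1 − B)(1 − p)^k, at p = 10% with independent panels:
- B = 40%: control 1 − 0.6 × 0.9 = 0.460. FMT 1 − 0.6 × 0.729 = 0.563 to 1 − 0.6 × 0.531 = 0.681. RR 1.22 to 1.48, false harm 5% to 19%.
- B = 50%: control 0.550; FMT 0.636 to 0.734. RR 1.16 to 1.34, false harm 4% to 15%.
- B = 80%: control 1 − 0.2 × 0.9 = 0.820; FMT 0.854 to 0.894. RR 1.04 to 1.09, false harm 2% to 5%.

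Correlation shrinks this further. With B = 40% and the Step 3 shares of 15.8% to 29.4%, the FMT share is 1 − 0.6 × 0.842 = 0.495 to 1 − 0.6 × 0.706 = 0.576, so the RR is 1.08 to 1.25.

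**The case against.** **Closer watching of treated infants has a stated reason.** Section 4.3 says that sepsis risk is highest soon after administration. This stands. The point concerns what enters the comparison, not how often an infant is sampled.

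**Both schedules bend to the infant's condition.** This also stands: 3–6 versus 1 is the scheduled contrast, not a guaranteed one. The asymmetry remains, because FMT infants have a repeat schedule by default and controls get further panels only when clinically required. Some checklist items may also be routine ward care in controls, but the article does not itemise them there.

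**The trial is a small pilot.** It reads estimates and intervals rather than p-values, classifies events by relatedness and warns against causal inference. Entry to phase two depends on SAEs (4.1), not on the Fisher test. This lowers the stakes, but an estimate-based reading still needs an undistorted relative risk.

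**Three stronger readings are tempting and not supported.**
- A reader might infer that FMT is bound to look worse through surveillance alone. The direction is expected, but the size rests on a per-panel rate and a correlation that the documents do not give.
- A reader might apply the relative risks of 2.4 to 5.3, or the 18–67% false significance, to the primary any-AE comparison. Those figures describe a marker-rise-only event with independent panels and no other AEs. Any other events, over a stay that section 5.3 says typically lasts several weeks, dilute the effect.
- A reader might infer that NEC is counted for only 72 h in FMT infants but without limit in controls. The abstract sets AE and SAE counting from intervention to discharge, so the 72 h list is post-procedure monitoring and does not truncate the endpoint.

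**Conclusion.** The concern holds as unequal scheduled ascertainment that may bias the safety comparison against FMT. It contradicts the equal observation claimed in section 2.2 and the parallel observation claimed in section 5.4.

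The bias is large for the specific comparison of marker-rise events: at an assumed 10% per panel, RR 2.7–4.7 at most and about 1.6–2.9 under correlation of 0.3–0.6. It is modest for the any-AE proportion: RR about 1.04–1.5 under an assumed 40–80% background and independent panels, and smaller under correlation. The expected direction is the same in every scenario examined.

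The stated mitigation does not cover the problem, because CRP panels and the cultures they trigger are part of what is scheduled unequally. The matter should be settled before data accrue, since an analysis cannot later build a commonly timed panel if the control panel may fall anywhere within 72 h.

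**What to change.** 1. Reconcile sections 2.2, 4.3 and 4.4, so that the article either describes equal observation or states the difference. Carry the same wording into the limitations in section 5.4.
2. In section 2.3.3, count isolated laboratory marker rises in the between-group comparison only from one panel per infant, timed in the same window after the index time in both arms. Report rises seen only on the additional FMT panels descriptively.
3. Keep culture-proven infection, NEC and all clinical AEs and SAEs in the comparison to discharge in both arms, however they were detected. Taking out cultures triggered by the extra FMT panels would remove proven sepsis from the safety comparison.
4. Record the same 72 h checklist items for controls, from bedside records, after their matching time point.

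**Cost.** One added control CRF page and short text edits, with no extra blood draws. Some FMT-arm laboratory data leave the comparative endpoint. With one panel counted per arm, the no-effect RR for marker rises returns to 1.0, and Fisher's test falsely shows harm in at most about 1.2% of trials for p up to 30%. The frequency of clinical monitoring in each arm remains a matter for the investigators.

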## 2. Experimental Design

### 2.1. Research Hypothesis

We hypothesize that prophylactic fecal microbiota transplantation in preterm infants is safe and well-tolerated, with an adverse event profile comparable to standard care.

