#### 2.3.3. Statistical Analysis

All analyses will be conducted on an intention-to-treat basis.

The primary endpoint is safety, defined as the incidence of adverse events (AEs) and serious adverse events (SAEs) during the observation period.

The proportion of patients experiencing at least one AE or SAE will be compared between groups using Fisher’s exact test. The chi-square test will be applied when its assumptions are met.

The incidence of specific AEs will also be compared using Fisher’s exact test. Relative risks (RRs) with two-sided 95% confidence intervals (CIs) will be calculated.

If the number of events per patient is analyzed, between-group comparisons will be performed using Poisson regression or negative binomial regression, depending on data dispersion.

Time to first AE, if applicable, will be analyzed using Kaplan–Meier estimates and compared using the log-rank test.

Continuous variables will be assessed for normality using the ShapiroWilk test. Normally distributed variables will be compared using Student’s *t*-test, and non-normally distributed variables using the Mann–Whitney U test.

Two-sided tests will be used throughout, with statistical significance set at α = 0.05. Estimates will be presented with two-sided 95% confidence intervals. Analyses will be performed using validated statistical software (e.g., R, Stata, or SAS); the exact software and version will be documented in the final report.

Given the limited sample size, the study is not powered for formal hypothesis testing of small effect sizes. Therefore, interpretation will focus primarily on effect size estimates and their 95% confidence intervals rather than solely on statistical significance. Clinically meaningful differences will be considered in the context of effect magnitude and precision.

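### In the 72 h after dosing, inflammatory markers are scheduled 3–6 times under FMT but need be drawn only once in controls, so the between-arm comparison of marker rises in that window is tilted against FMT

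*Protocol article*

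**What the plan says.** All references are to the protocol article.

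- **FMT arm (4.3).** After a panel before the first dose, markers are drawn "no later than 6–12 h after administration of FMT2, then every 12–24 h up to 72 h after FMT", depending on the infant's condition. The same section adds: "A blood culture will be taken in the event of a significant increase in inflammatory parameters".
- **Control arm (4.4).** After the matching time point, which is given as a day of life without a clock time, markers are drawn "at least once within 72 h of day 6, or more frequently if the patient’s clinical condition requires it". The attending physician judges that need.
- **What counts as an event.** In controls, section 4.4 records deviations such as "appearance of symptoms of infection or increase in inflammation indicators". Section 5.1 puts "deterioration in general condition, appearance of symptoms of infection, and increase in inflammation indicators" into the primary outcome.
- **How the arms are compared (2.3.3).** Infants with any AE or SAE are compared by Fisher's exact test. In addition, "The incidence of specific AEs will also be compared using Fisher’s exact test", with relative risks and 95% confidence intervals.
- **What is said about observation.** Section 2.2 describes controls as "subject to the same hospital observation but without undergoing any medical/therapeutic intervention other than the collection of biological material". Section 5.4 calls the observation parallel and names CRP and blood cultures among the objective measures that limit detection bias.

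**The concern.** A symptom-free marker rise is seen only if blood is drawn. One arm has several scheduled draws in the window and the other has one guaranteed draw, so the first will tend to show more such rises even if FMT does nothing. Blood cultures prompted by a rise can carry the imbalance further.

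The hypothesis in section 2.1 is that FMT "is safe and well-tolerated, with an adverse event profile comparable to standard care", and section 2.3.1 intends the adverse event rates for planning a later randomized trial. An excess that comes from more frequent sampling could be read as an FMT signal and would distort those rates. The limitations in section 5.4 do not cover this. They attribute detection bias to the open-label design and to subjective endpoints, and treat as safeguards the very measures that are sampled unequally.

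**Working it through.** The document gives no figure of its own to reproduce: section 2.3.1 reports no formal sample size calculation.

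**Step 1. Count the panels.** Inputs from section 4.3: first draw f = 6–12 h after the second dose, interval g = 12–24 h, end at 72 h. Number of panels = floor((72 − f)/g) + 1.

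- f = 6, g = 24: 6, 30, 54 h, so 3
- f = 12, g = 24: 12, 36, 60 h, so 3
- f = 6, g = 12: 6, 18, 30, 42, 54, 66 h, so 6
- f = 12, g = 12: 12, 24, 36, 48, 60, 72 h, so 6

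The range is 3–6, or 60–120 panels in 20 infants. Controls need at least 1 each, so at least 20 in 20. Counting the 72 h from the first dose (66 h after the second) leaves the range at 3–6.

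**Step 2. Illustrate the effect within 72 h, with no FMT effect.** The document gives neither the chance p of a symptom-free rise per panel nor the within-infant correlation ρ. Both are assumed: p = 5–20%, ρ = 0–0.8, equal in both arms.

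- ρ = 0: P(at least one rise in k panels) = 1 − (1 − p)^k.
- ρ > 0 (beta-binomial): 1 − Π (b + i)/(a + b + i) for i = 0 to k − 1, with a = p(1 − ρ)/ρ and b = (1 − p)(1 − ρ)/ρ.

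Apparent risk ratio against one control panel, over p = 5–20%:

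| ρ | 3 FMT panels | 6 FMT panels |
|---|---|---|
| 0 | 2.44–2.85 | 3.69–5.30 |
| 0.5 | 1.64–1.78 | 2.04–2.34 |
| 0.8 | 1.25–1.29 | 1.38–1.47 |

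Worked case, p = 10% and ρ = 0.5, so a = 0.1 and b = 0.9:

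- 3 panels: 1 − 0.9 × (1.9/2) × (2.9/3) = 17.4%, or 3.47 of 20 infants
- 6 panels: multiplying the product further by (3.9/4) × (4.9/5) × (5.9/6) gives 22.3%, or 4.47 of 20
- 1 panel: 10%, or 2.00 of 20

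The ratio is 1.7–2.2. If controls in practice have two panels, the ratio over all the assumed values is 1.07–2.72. If rises persist through the whole 72 h, it tends to 1.

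**Step 3. Extend to discharge.** The abstract runs the endpoint to discharge, and section 5.3 expects stays of several weeks. Suppose 50% of infants have a later marker rise anyway (assumed). Then P = 0.5 + 0.5 × P(72 h):

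- FMT: 0.5 + 0.5 × 0.174 = 58.7% to 0.5 + 0.5 × 0.223 = 61.2%
- Control: 0.5 + 0.5 × 0.10 = 55.0%
- Ratio: 58.7/55.0 = 1.07 to 61.2/55.0 = 1.11

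**Step 4. Effect on the proportion with any AE.** Here P = q + (1 − q) × P(72 h), where q is the assumed share of infants with another AE.

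- q = 50%: 58.7–61.2% against 55.0%, that is +3.7 to +6.2 points
- q = 80%: 83.5–84.5% against 82.0%, that is +1.5 to +2.5 points

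In 20 infants this is 20 × 0.015 = 0.3 to 20 × 0.062 = 1.2 infants.

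**The case against.** **The ratios describe the wrong window.** Events accrue to discharge in both arms, and a ratio built on 72 h overstates what the final table would show. This stands. A reader might infer from 1.25–5.3 that the primary result itself is inflated to that extent. The document does not support this: the figures apply only to marker rises within 72 h, and steps 3 and 4 show how far they shrink outside it.

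**The per-panel rates are invented.** They are assumptions, and higher rates shrink the ratio: at p = 50% and ρ = 0.5 it is about 1.38 (3 panels) to 1.55 (6 panels). High rates cannot be excluded, because the CRP cutoff in section 2.3.6 lies at the bottom of the normal range stated there. One control panel is also a floor, not a forecast. The size is therefore unknown, but the direction does not change.

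**The FMT draws may be discretionary.** The reference to the infant's condition most naturally selects an interval within 12–24 h. If every draw after the first were optional, the count of 3 would no longer be guaranteed. FMT infants would still have a default schedule that controls lack.

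**Closer monitoring after FMT is right, and over-detecting harm is the safer error.** Agreed. Section 4.3 gives the sepsis risk as the reason. A reader might infer that FMT infants are sampled too often, or that clinically evident infection is missed in controls. Neither follows: the extra panels are justified, and symptomatic events are recorded in both arms. Nor is the step to phase two affected by this comparison, since section 4.1 ties it to SAEs.

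**An analysis plan could deal with it.** It could pair each control panel with the nearest FMT panel from recorded draw times, which would help. It cannot choose when the control panel was drawn, and section 4.4 leaves the hour open within 72 h of a day that has no clock time. That must be settled before sampling.

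**Conclusion.** The point holds for marker rises in the 72 h after dosing. The two schedules are stated outright and are unequal, the event they detect is part of the primary safety outcome, and the arms are compared on it. For this component, the description of controls as under the same observation is not met. The bias runs against FMT.

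The size is unknown. About 1.25–5.3 is an illustration for the 72 h window, resting on assumed per-panel rates and correlations, on equal true risk in both arms, on exactly one control panel, and on the reading that gives 3–6 FMT panels. Over the whole stay the worked case falls to about 1.07–1.11 under a further assumption, and the effect on the any-AE proportion is small.

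A reader might also infer that the unstated culture threshold, or the absence of a culture rule for controls, is an error. A condensed article may simply omit these, so no such claim is made. Severity is minor to moderate.

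**What to change.** Name one anchor panel in both arms, with a stated window: for example 30 h after the second dose, and 30 h after a stated clock time for the control matching point. From any first FMT draw at 6–12 h, 30 h is one step of 18–24 h away (30 − 12 = 18, 30 − 6 = 24). It therefore fits the existing rule and normally adds no draw. An infant sampled 12-hourly from 12 h has draws at 24 and 36 h, each 6 h away, and relies on the window.

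Then:

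- Base the between-arm comparison of 72 h marker-rise events on the anchor panel.
- Add a secondary comparison that includes panels ordered for clinical signs, but not repeats prompted only by a rise on an extra FMT panel.
- Record at the draw whether each panel is anchor, extra scheduled or clinically indicated.
- Keep all extra FMT panels. Report every event and culture they reveal as FMT-arm safety data, flagged as found by extra surveillance.
- Report panels and cultures per infant by arm.

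The cost is an amendment to the approved protocol, one data field and two descriptive table rows. There are three downsides. One FMT draw time becomes fixed. The anchor comparison is less sensitive to short-lived rises. Postnatal age stays unaligned, since FMT can be given from day 3 while controls are anchored at day 6.

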#### 2.3.6. Temporary Exclusion Criteria

Criteria for temporary postponement of microbiota administration (study group) and postponement of the matching time point for administration of intestinal microbiota doses (control group) if, prior to FMT or on day 6 of life, at least one of the following occurs as identical for microbiota administration and up to day 14 of life:Oral feeding intolerance: (assessed by the qualifying physician on the day of the planned FMT) if any of the following are present:
-Painful abdominal distension and/or visible intestinal loops.-Blood in the stool.-Increased gastric residuals:
Two consecutive episodes exceeding >50% of the volume of the previous portion.Two or more consecutive episodes of retention/bilious or duodenal residuals/emesis—when these episodes are not related to anxiety, delayed stool passage, the possibility of swallowing blood during delivery or from damaged nipples, incorrect positioning of the gastric catheter, bleeding from the nasal cavity.Increased gastric residual volume is not defined as a volume of up to 2 mL if the newborn receives a feeding portion of 1–2 mL.

Suspected NEC based on Bell’s criteria.Antibiotic therapy during planned FMT administration.Clinical/laboratory/radiological signs of infection—if at least one of the following clinical signs and/or more than one laboratory and/or radiological sign is present:
-Clinical symptoms of infection:
Hemodynamic instability: hypotension, tachycardia, peripheral circulation disorders (according to age norms), thermoregulation disorders, and fever > 38 °C, hypothermia < 36 °C.Apathy, lethargy, and convulsions.Apnea and deterioration of respiratory efficiency.
-Laboratory symptoms of infection:
Elevated inflammation parameters: leukocyte count< 5 and >30 thousand/μL up to 48 h and <5 and >20 thousand/μL > 48 h; left shift in neutrophil differential I:T > 0.2 for >34 h and >0.16 for <34 h.Platelet count < 50 K, coagulopathy.CRP > 0.05 mg/L (normal range < 0.05–1 mg/L); PCT (>72 h) > 0.5–1 ng/mL (normal range 0.5–1 ng/mL).Positive cultures of normally sterile body fluids.
-Radiological signs of infection, including systemic infection, e.g.,
Gallbladder bed edema.Unexplained pulmonary hypertension suddenly detected by echocardiography.

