## 4. Detailed Procedure

### 4.1. Transplant Recipients Procedures

FMT will be administered to patients in the study group who meet the inclusion criteria and do not meet the exclusion criteria, in the form of a deep rectal infusion, in a volume of 5 mL, twice at 6 h intervals, between 3 and 6 days after birth and/or up to 14 days in patients who experience temporary contraindications to the use of FMT or in patients who will be transferred to our center for treatment from an external facility.

In the first phase of the experiment, 10 patients from the study group born between 28 0/7 and 36 6/7 will undergo the procedure. All adverse effects of the therapy will be monitored and documented on an ongoing basis. If no serious adverse events (SAEs) occur, we will include another 10 patients born between 24 0/7 and 27 6/7 in the study (phase two of the experiment).

A serious adverse event (SAE) is defined as any medical event that, at any dose, meets at least one of the following criteria:Leads to death.Is life-threatening to the participant.Requires hospitalization or prolongs hospitalization.Leads to permanent or significant impairment of function or disability.A detailed description of the monitored parameters is provided below.

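### Section 4.3 permits the second FMT dose after any short-lived postponement sign that follows the first, with no exception for a sign that was life-threatening

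*Protocol article*

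**What the plan says.** Section 4.1 plans the product "in a volume of 5 mL, twice at 6 h intervals". Section 4.3 covers an infant who develops a sign after the first dose: "If any of the above-described criteria for temporary postponement of microbiota administration occur between FMT1 and FMT2 but resolve within 6 h" and there is no return of the sign over a further six hours, "the second dose of microbiota (FMT2) may be administered". The signs are not redefined there. They are the Section 2.3.6 criteria for postponing a dose, which range from gastric residuals and laboratory values to suspected NEC, hypotension, convulsions and "Apnea and deterioration of respiratory efficiency".

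Section 4.1 defines a serious adverse event by four criteria, one of which is "Is life-threatening to the participant". The dosing consequence it attaches to such events is at cohort level: "If no serious adverse events (SAEs) occur, we will include another 10 patients born between 24 0/7 and 27 6/7 in the study". Section 4.3 lists among the items assessed over 72 hours "Number of serious adverse events (SAEs), e.g., death, serious threat to health and/or life, and/or deterioration of health", but does not connect that item to the second dose.

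**The concern.** The Section 2.3.6 list mainly decides whether an infant is fit to receive a planned dose. Section 4.3 reuses it once the infant has been exposed, when the same sign may be a reaction to the product. A convulsion two hours after the first dose is then cleared by essentially the same test as one that occurred before any dose.

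The primary endpoint is safety, and Section 4.3 itself places the highest sepsis risk in the first six hours after administration, which is also the planned interval between doses. So the rule governs the period the authors regard as most dangerous. At stake is re-exposure of an infant who has just had a short but life-threatening episode, under a rule that gives the physician no seriousness criterion to apply.

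**Working it through.** The plan gives no figure to reproduce on this point. The check sets the provisions side by side, with one piece of timing arithmetic.

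1. **Scope of the rule.** Section 4.3 speaks of *any* of the postponement criteria. Hypotension, convulsions and apnea are on the Section 2.3.6 list, so they are covered.

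2. **Overlap with serious events.** Each of these can be life-threatening, and a life-threatening event is serious under Section 4.1. One episode can therefore be both a postponement sign and a serious adverse event.

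3. **Search for an exception.** None of Sections 2.3.5, 2.3.6, 4.1, 4.2 or 4.3 says that a serious or life-threatening event after the first dose bars the second.

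4. **Comparison with the pre-exposure test.** Section 2.3.6 requires reassessment after at least 6 h and then 6 h without recurrence. Section 4.3 requires the same and adds that the sign must have cleared within 6 h. That cap is stricter on duration but says nothing about severity.

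5. **Timing.** Let the sign begin *t* hours after the first dose, with 0 < *t* < 6, and assume the reassessment clock starts at onset.
 - Earliest permitted second dose = *t* + 6 h (reassessment) + 6 h (no recurrence) = *t* + 12 h.
 - Range: 0 + 12 = 12 h to 6 + 12 = 18 h after the first dose, against the planned 6 h. The delay is 12 − 6 = 6 h to 18 − 6 = 12 h.
 - Example: onset at 2 h, clear at reassessment at 8 h, no recurrence to 14 h; dosing is then permitted.

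 This describes when the rule allows dosing. It does not measure harm.

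6. **Safeguards tested against a brief life-threatening apnea, convulsion or hypotensive episode.**

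| Provision | Does it bar the second dose? |
|---|---|
| Antibiotic exclusion, including 24 h after the course (Section 2.3.5) | Only if antibiotics are given |
| Wait of 24–48 h after a culture (Section 2.3.6) | Delays it, and only if a culture is taken; Section 4.3 triggers a blood culture by a significant rise in inflammatory markers |
| Examination and follow-up laboratory tests (Section 2.3.6); re-check before dosing (Section 4.2) | Only if a contraindication is still present; a cleared episode passes |
| Continuous monitoring: "Therefore, after the procedure, the patient will be continuously monitored" | No; it detects the event but sets no dosing consequence |
| Trained physicians decide on administration (Section 2.3.2); the permissive *may* in Section 4.3 | Only if the physician chooses to withhold |

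For an episode that clears without antibiotics or a culture, only the last row remains.

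**The case against.** The strongest reply is that this is a journal article condensing a fuller protocol, and that rules for stopping treatment in an individual infant are commonly left to that document. This stands against any inference that the trial has no withdrawal rule; the article cannot support that inference and it is not made here. It does not dispose of the point, because Section 4.3 states a positive re-dosing rule with its own thresholds, and that rule as worded reaches too far.

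Second, the wording is permissive. It sets minimum conditions and obliges no one to dose, and a trained physician may well withhold. That is correct and is a main reason for the low severity. But the text offers no seriousness criterion to guide the choice.

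Third, the uncovered case is narrow. The event must fall between the doses, threaten life, clear within six hours, not recur for six more, and involve neither antibiotics nor a culture. This is conceded.

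A reader might go further in three ways that the documents do not support:

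- **The phase gate contradicts the individual rule.** It does not. The gate decides whether to open a more vulnerable cohort, while Section 4.3 decides dose timing in one infant; the first may reasonably be stricter.
- **Up to 20 infants are affected, or exposure is doubled.** Twenty (10 + 10) is everyone planned to receive FMT, not the number who would meet the gap. Two doses of 5 mL, or 10 mL, is simply the planned regimen.
- **Every serious adverse event should bar the second dose.** Some Section 4.1 criteria, such as prolonged hospitalization, cannot be judged within hours. Only the life-threatening criterion is workable at that moment.

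Finally, a bar that ignores cause will sometimes withhold a dose after an event due to prematurity alone. That is a real cost. It is accepted because relatedness can seldom be settled in the hours available.

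**Conclusion.** The point holds as a minor, inexpensive improvement. As written, Section 4.3 does not bar a second dose after a brief life-threatening apnea, convulsion or hypotensive episode that follows the first dose and needs no antibiotics or culture; only physician discretion does.

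The frequency of such episodes cannot be estimated, since the documents give no rate. No sample size, test or endpoint definition depends on the point. The conclusion rests on reading *any* literally and on the provisions in the published article alone.

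**What to change.** Add one sentence to Section 4.3: the second dose is not given to an infant who, after the first, has an event judged at that time to be life-threatening in the sense of Section 4.1, whatever its suspected cause. Keep the existing deferral rule, including its six-hour limit on resolution, for all other signs.

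The cost is that some infants, presumably few, receive one 5 mL dose only. They remain in the study group under the intention-to-treat principle of Section 2.3.3.
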